### Sample size and statistical analysis

To test the primary hypothesis, 103 patients will be necessary with 80% power and 5% type 1 error, considering 50% of group 1–2 (low risk), 50% of group 3 (high risk), 16% of likelihood of VT recurrences at 12 months in low-risk patients and 44% of likelihood in high-risk patients with HR (high risk/low risk of recurrences) of 2.75 (Cox PH, 2-sided equality).

All applicable statistical tests will be 2-sided and will be performed using a 5% significance level. Continuous variables will be reported as mean ± standard deviation, or median (range or interquartile range if data are skewed) if not normally distributed; these variables will be compared using Student’s t-test if normally distributed, Aspin-Welch test if normally distributed with unequal variance demonstrated using Variance-ratio F-test, or Mann–Whitney U test if not normally distributed. Categorical variables will be expressed as total number (percentage) and will be compared by chi-squared test. As far as the primary endpoint, data will be analyzed according to the intention-to-treat principle. Survival free from ventricular arrhythmia, will be evaluated using a time-to-first-event analysis with the Logrank test and the Kaplan–Meier cumulative event rate. A multivariable Cox proportional hazards model will be performed to investigate the effects of baseline characteristics in predicting ablation results.

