## Methods

### Study hypothesis and primary endpoint

Our hypothesis is that a comprehensive preprocedural individual characterization of the myocardial substrate via a CMR scan, and its integration within the mapping system can significantly improve technical intervention and patient outcome. The primary objective is to analyze the outcome of CMR guided/aided approaches of VT ablation in terms of effectiveness at 12 months in comparison to a control group (standard of care VT ablation). The primary endpoint is defined as any VT recurrences during a 12-months follow-up (not including the first month). VT episodes will be considered as recurrences if sustained (more than 30 s) or requiring appropriate ICD intervention and will be detected during outpatient clinic evaluation through an ICD interrogation.

Pre-specified group subanalyses will compare in terms of the primary endpoint:Patients with structural heart disease of ischemic originPatients undergoing endocardial-substrate only ablation

Secondary objectives are shown in Table 1.

**Table 1 Tab1:** Secondary endpoints

Secondary endpoints
Health-related quality of life changes
Procedural time (introducer in-introducer out)
Fluoroscopy duration
X-ray exposure
Radiofrequency time
Number of RF applications
VT inducibility at the end of ablation with number of residual VTs
Appropriate and inappropriate ICD interventions (ATP or shocks) anytime and after 1 month
Rate of patients with contraindication to CRM or with poor CMR imaging
Hospital admission for cardiac causes
VT storm anytime and after 1 month
Composite endpoint including death at any time, VT storm and appropriate ICD shock after 1 month of treatment
*Complications during 12-month follow-up*
Death (related or not to the procedure)
Myocardial infarction
Stroke or transient ischemic attack (TIA)
Other thromboembolic events
Cardiac perforation or tamponade
Vascular complications
Prolonged or repeat hospitalization
Heart block
Pericarditis requiring intervention
Pneumothorax
Pulmonary edema
Hepatic injury
Abdominal issues

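### The planning hazard ratio of 2.75 is the risk ratio 44%/16%; under the Cox model named, those rates imply 3.33, so the rates, HR, 80% power and N = 103 are not one consistent set

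*Protocol article*

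**What the plan says.** The protocol article, Sample size and statistical analysis, gives the whole calculation in one sentence. It states that "103 patients will be necessary with 80% power and 5% type 1 error". Half of the patients are taken to be in Groups 1–2 pooled, labelled low risk, and half in Group 3, labelled high risk. The recurrence assumptions read "16% of likelihood of VT recurrences at 12 months in low-risk patients and 44% of likelihood in high-risk patients with HR"; the value given for that hazard ratio, Group 3 relative to Groups 1–2, is 2.75. The method is named as a two-sided Cox proportional-hazards test of equality. The same section makes time to first event, compared by the log-rank test, the analysis of survival free from ventricular arrhythmia.

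Under Study hypothesis and primary endpoint, the event is defined as "any VT recurrences during a 12-months follow-up (not including the first month").

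**The concern.** The two rates and the hazard ratio are presented together as one set of assumptions under one model, yet the value called a hazard ratio equals the quotient of the two cumulative risks. Risk ratio and hazard ratio are close only when events are rare, and at 44% they are not.

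This sentence is the only justification printed for the size of the primary comparison. As it stands, a reader cannot tell which effect the trial was designed to detect. If the result is null, it would be unclear how much power there was against a hazard ratio of 2.75, or against a fall from 44% to 16%.

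**Working it through.** **Inputs**, all from Sample size and statistical analysis: two-sided alpha 0.05 (z = 1.960), power 80% (z = 0.842), 50:50 split, risks 0.16 and 0.44, HR 2.75, N = 103. The article states no loss to follow-up, and none is assumed here.

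**Step 1: reproduce 103.** Cox/Schoenfeld formula:

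- Events d = (1.960 + 0.842)² / (0.5 × 0.5 × [ln HR]²). With HR 2.75, d = 30.68.
- Mean event probability = (0.16 + 0.44)/2 = 0.30.
- N = 30.68/0.30 = 102.27, rounded up to 103.
- At N = 103, expected events are 103 × 0.30 = 30.9 and power is 80.3%.

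The stated figure reproduces, so the division is correct. The question is whether the inputs belong together.

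**Step 2: the HR that the rates imply.**

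- 0.44/0.16 = 2.75, the ratio of risks.
- Under proportional hazards, HR = ln(1 − 0.44)/ln(1 − 0.16) = ln(0.56)/ln(0.84) = 3.33, whatever the shape of the baseline hazard.
- Excluding the first month does not alter this. For two risks over the same window, the HR is still the ratio of log survival probabilities.

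**Step 3: the rates that HR 2.75 implies.**

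- Holding 16% in Groups 1–2: Group 3 = 1 − 0.84^2.75 = 38.1%, mean 27.0%.
- Holding 44% in Group 3: Groups 1–2 = 1 − 0.56^(1/2.75) = 19.0%, mean 31.5%.

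**Step 4: N and power for each consistent set.** Formula power is Φ(√events × 0.5 × ln HR − 1.960), with events = 103 × mean event probability. The last column is a log-rank simulation with 52 and 51 patients and exponential event times.

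| Design assumption | Group 1–2 / Group 3 | HR | Events at 103 | N for 80% (formula) | Power at 103 (formula) | Power at 103 (simulated) |
|---|---|---|---|---|---|---|
| The two rates | 16% / 44% | 3.33 | 30.9 | 21.74/0.30 = 72.5, so 73 | 91.6% | 89% |
| HR 2.75, 16% held | 16% / 38.1% | 2.75 | 27.9 | 30.68/0.2704 = 113.4, so 114 | 76.1% | 73% |
| HR 2.75, 44% held | 19.0% / 44% | 2.75 | 32.5 | 30.68/0.3150 = 97.4, so 98 | 82.2% | 80% |

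By the formula that reproduces 103, none of the three sets returns 103 at 80%.

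**Step 5: sensitivity to the formula.** For the two stated rates, the Freedman formula gives N = 91 and 84.8% power at 103. Simulating the log-rank test at N = 73 gives about 76%, so 73 is somewhat optimistic.

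**The case against.** The strongest reply is that the error does no harm. If 2.75 is merely 44/16, it was never chosen independently, so the real assumptions are the two rates. On those rates 103 patients give 85% to 92% power depending on the method, more than was promised. Endpoint, test, alpha and N are unaffected. This stands, and it limits the severity. It does not make the sentence right: a Cox calculation is printed with a hazard ratio that its own rates contradict.

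A reader might infer that the trial is under-powered, or that the stated 80% fits no reading. The documents do not support either. Power falls below 80% by formula only if HR 2.75 is held together with the 16% rate. Holding the standard-of-care rate of 44%, an equally natural way to state a design, gives 82% by formula and about 80% by simulation, almost exactly what is claimed.

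A reader might equally infer that 73 patients would do and the trial is well over-sized. The simulation at 73 and the Freedman figure of 91 both show that the excess is smaller than 103 against 73 suggests.

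The figure of 103 can also be reached another way: a two-proportion comparison needs 41 per group, 82 in all, and 82/0.80 = 102.5, so 103 with an assumed 20% loss. The article states neither that test nor any loss, and it names the Cox model, so this route cannot be credited.

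**Conclusion.** Wrong as written, moderate severity. A ratio of 12-month risks is labelled a hazard ratio and combined with a mean event rate that belongs to a different hazard ratio (3.33).

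The direction of the consequence depends on which input was meant, and the article does not say. It is conservative if the rates govern, roughly neutral if HR 2.75 is paired with 44%, and a shortfall of about 4 points by formula (7 simulated) if HR 2.75 is paired with 16%. Across these readings power at 103 runs from about 73% to 92%.

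These figures rest on proportional hazards, the article's 50:50 split between Groups 1–2 and Group 3, and complete 12-month follow-up. The identity 44%/16% = 2.75 and the implied HR of 3.33 do not depend on the split or on follow-up.

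**What to change.** Keep 103. State whether the two rates or the hazard ratio are the design assumption, make the other agree (HR 3.33 if the rates govern), and restate the power at 103 for that choice. If the rates govern, a sentence such as this would do:

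> Recurrence at 12 months of 16% in Groups 1–2 and 44% in Group 3 corresponds to a hazard ratio of 3.33. With equal groups and a two-sided 5% test, 103 patients give about 89–92% power. If the hazard ratio is 2.75, power is about 73–82%, depending on whether the 16% or the 44% rate is held fixed.

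The cost is one corrected sentence. No extra patients are needed, and endpoint, test and analysis stay as they are.

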All patients who give informed consent for participation and fulfill the inclusion eligibility criteria will be consecutively enrolled (Inclusion and exclusion criteria are respectively shown in Tables 2 and 3). They will subsequently be evaluated for eligibility to CMR and CT. Patients with clinical or device-related contraindications to CMR or CT or with image quality deemed suboptimal for postprocessing will be assigned to Group 3 and undergo standard of care ablation. The other patients will be randomized in a 1:1 fashion to either Group 1 or 2 using a web-based platform. The scientific coordinator of the study or a delegate should be the unique responsible of randomization and will be contacted upon all new recruitments. LGE-CMR data obtained by 1.5 or 3 T CMR and multi-detector cardiac tomography (MDCT) data obtained using a 64 to 128 slice CT scanner will be processed with a specific commercial software (ADAS 3D, Galgo Medical, Barcelona, Spain). In Group 1, ablation will be performed based only on cardiac imaging information processed by the abovementioned software without electroanatomical mapping. A so-called anatomical approach is consistent with a previous observation [9] that ablation of channels only can be effective in preventing VA recurrences. In Group 2 ablation procedure will be based on information derived from both imaging and electroanatomic mapping data, but electrical CCs will remain as the final ablation target. Finally, Group 3 will be treated with standard ablation according to current clinical practice based on electroanatomic mapping (EAM). (Fig. 1).

**Table 2 Tab2:** Study inclusion criteria

Inclusion criteria
Indication for VT ablation in patients with structural heart disease (indications according to the 2015 ESC Guidelines for the management of patients with ventricular arrhythmias and the prevention of sudden cardiac death);
Structural heart disease (clinical history, ECG, multimodality imaging) involving the left ventricle
Signed informed consent;

**Table 3 Tab3:** Study exclusion criteria

Exclusion criteria
Age < 18 years;
ICD not already implanted nor expected within 1 month;
High probability of non-adherence to the follow-up requirements (due to social, psychological, or medical reasons);
Inability to give written informed consent;
Pregnancy (suspected or confirmed);
Acute coronary syndrome or PCI in the previous 30 days

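### If deaths are censored, the planned Kaplan–Meier rate overstates the 12-month probability of VT recurrence, slightly and unevenly between groups

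*Protocol article*

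**What the plan says.** In the protocol article, under *Study hypothesis and primary endpoint*, the endpoint is given as "The primary endpoint is defined as any VT recurrences during a 12-months follow-up (not including the first month"; the exclusion of month 1 closes the definition. What counts as a recurrence follows: "VT episodes will be considered as recurrences if sustained (more than 30 s) or requiring appropriate ICD intervention". Death is not a component. It appears in Table 1 only, as an item in the complications list and in a secondary composite: "Composite endpoint including death at any time, VT storm and appropriate ICD shock after 1 month of treatment".

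Under *Sample size and statistical analysis*, the paragraph on the primary endpoint invokes the intention-to-treat principle and then states: "Survival free from ventricular arrhythmia, will be evaluated using a time-to-first-event analysis with the Logrank test and the Kaplan–Meier cumulative event rate".

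Under *Trial design*, Group 3 is filled by suitability for imaging: "Patients with clinical or device-related contraindications to CMR or CT or with image quality deemed suboptimal for postprocessing will be assigned to Group 3". Randomisation covers only the remaining patients: "The other patients will be randomized in a 1:1 fashion to either Group 1 or 2 using a web-based platform".

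The article gives no mortality figure, overall or by group.

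**The concern.** A Kaplan–Meier event rate estimates the actual probability of an event only if censored patients could still have that event later. A patient who dies cannot have VT. With deaths censored, one minus the Kaplan–Meier estimate describes recurrence in a setting where nobody dies, and this exceeds the proportion of patients who will in fact have a recurrence.

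The excess grows with the VT hazard as well as with mortality. Even with the same mortality everywhere, it is therefore larger in the group with more recurrences, which under the planning assumptions is Group 3. At stake are the reported 12-month rates and the absolute difference between the CMR groups and standard care.

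The wording of the analysed variable adds a smaller difficulty. It speaks of survival and of ventricular arrhythmia, whereas the endpoint is VT meeting a stated definition after a one-month blanking period.

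**Working it through.** **Inputs from the article.** 12-month recurrence of 16% (Groups 1–2) and 44% (Group 3); hazard ratio 2.75; 50:50 split; 80% power; two-sided 5%.

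**Assumed inputs.** 12-month mortality of 3% to 10% in Groups 1–2 and 5% to 20% in Group 3. These are illustrations, because the article gives no figure.

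**The plan's own figure.** The article states "103 patients will be necessary with 80% power and 5% type 1 error", by the method "Cox PH, 2-sided equality". Schoenfeld's formula gives

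events = (1.960 + 0.842)² / (0.25 × (ln 2.75)²) = 30.68.

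The mean event probability is (0.16 + 0.44)/2 = 0.30, so N = 30.68/0.30 = 102.3, rounded up to 103. The figure reproduces. The choice of estimator for the event rate does not enter it.

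**Size of the overstatement.** Take constant cause-specific hazards over 12 months, and treat 16% and 44% as the rates that Kaplan–Meier would show with deaths censored. The blanking month is ignored for simplicity. Then

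- VT hazard λ = −ln(1 − Kaplan–Meier rate): 0.1744 in Groups 1–2 and 0.5798 in Group 3;
- death hazard μ = −ln(1 − mortality): 0.0513 at 5%, 0.1054 at 10%, 0.2231 at 20%;
- cumulative incidence = λ/(λ + μ) × (1 − exp(−(λ + μ))).

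For example, at 5% mortality:

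- Groups 1–2: 0.1744/0.2256 × (1 − 0.84 × 0.95) = 0.773 × 0.202 = 15.6%.
- Group 3: 0.5798/0.6311 × (1 − 0.56 × 0.95) = 0.919 × 0.468 = 43.0%.

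| Assumed mortality, Groups 1–2 / Group 3 | Incidence, Groups 1–2 | Incidence, Group 3 | Gap (points) | Inflation of the 28-point gap (points) |
|---|---|---|---|---|
| 0% / 0% | 16.0% | 44.0% | 28.0 | 0 |
| 5% / 5% | 15.6% | 43.0% | 27.4 | 0.6 |
| 10% / 10% | 15.2% | 42.0% | 26.8 | 1.2 |
| 10% / 5% | 15.2% | 43.0% | 27.8 | 0.2 |
| 3% / 5% | 15.8% | 43.0% | 27.2 | 0.8 |
| 5% / 10% | 15.6% | 42.0% | 26.4 | 1.6 |
| 5% / 20% | 15.6% | 39.9% | 24.3 | 3.7 |
| 3% / 20% | 15.8% | 39.9% | 24.1 | 3.9 |

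Kaplan–Meier is too high by 0.2 to 0.8 points in Groups 1–2 and by 1.0 to 4.1 points in Group 3.

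**The case against.** **The effect is small and the test is untouched.** This stands. With deaths censored, log-rank and Cox address the cause-specific hazard, so deaths do not invalidate the primary comparison. The exclusions in Table 3 (NYHA IV, stage 5 kidney disease, Child–Pugh C, illness limiting survival to under a year) hold mortality down. At equal mortality of 5% to 10% the gap moves by about a point out of 28.

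**The handling of death may be set out in a statistical analysis plan that is not shown.** That is possible, and silence about death would not by itself be a point. But the article does name an estimator for the event rate. For an endpoint that leaves death out, that estimator does not give the actual probability of recurrence.

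**A reader might infer that mortality differs between the groups, so that the rates are biased in favour of CMR by 2 to 4 points.** The article does not support this. Its high-risk label for Group 3 refers to VT recurrence. Assignment by contraindication or poor images makes higher mortality plausible, and no more than that. The larger figures in the table come entirely from assumed unequal mortality.

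**A reader might also infer that the analysis section sets a different primary endpoint, one that counts death or any ventricular arrhythmia.** Counting death would matter: at 5% mortality in both groups the rates would be 1 − 0.84 × 0.95 = 20.2% and 1 − 0.56 × 0.95 = 46.8%. But the sentence follows directly on a reference to the primary endpoint, the sample-size text beside it speaks of VT recurrences, and the article uses VA and VT interchangeably elsewhere. This is loose wording to be tidied. Nor can both complaints hold together: if death counted as an event, the overstatement from censoring it would disappear.

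**Conclusion.** The point holds for the reported event rates. With death outside the endpoint and censored, the Kaplan–Meier rate overstates the 12-month probability of VT recurrence, and at equal mortality it does so more in the group with the higher VT hazard. The gap of 28 points is inflated by about 0.6 to 1.2 points at equal mortality of 5% to 10%, and by up to about 4 points if Group 3 mortality were as high as 20%.

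These sizes rest on constant hazards, on reading 16% and 44% as Kaplan–Meier values, and on assumed mortality. The amount depends on how mortality falls across the groups: with 10% in Groups 1–2 and 5% in Group 3, the inflation nearly vanishes. As far as deaths are concerned, the log-rank and Cox comparison remains valid for the cause-specific hazard, and 103 stands. Confounding from the non-random allocation to Group 3 is a separate matter.

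**What to change.** In *Sample size and statistical analysis*:

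1. Name the analysed variable as time to first VT recurrence, as defined under *Study hypothesis and primary endpoint*, with VT in the first month not counted.
2. Replace the Kaplan–Meier cumulative event rate with the Aalen–Johansen cumulative incidence, with death as the competing event. Keep all patients in the intention-to-treat set. A day-30 landmark is not needed and would drop early deaths.
3. Keep log-rank and Cox, and label them as the cause-specific comparison.

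An analysis of death or VT as one event is an optional sensitivity analysis.

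The cost is a change of wording and a standard routine. No additional patients or visits are needed, and deaths are already recorded as a complication. Reported event rates will be slightly lower, which should be kept in mind when they are set beside Kaplan–Meier rates from other studies.

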## Discussion

Integration of high-definition myocardial substrate data acquired via imaging techniques such as CMR and MDCT has already been proved as a feasible and potentially effective solution for VT ablation, even in complex and cutting-edge scenarios [9, 12–14]. However, MDCT-only approaches, in which myocardial wall thickness maps can identify "CT-channels" [15] where VT functional isthmuses can be located, showed poor performance [16] when compared to CMR in correctly identifying the arrhythmogenic substrate, especially when entirely subendocardial.

The mainstay of our proposal is represented by real time integration, alignment, and synchronization of 3D-meshes, containing anatomical data obtained from MDCT, and substrate data derived from postprocessed CMR, with the tridimensional references of the electroanatomical mapping suite, allowing operators to effectively navigate such meshes irrespectively of the presence of a standard complete LV EAM.

As far as CMR is concerned, single-center experiences have already shown that an approach where MRI derived information is used alongside EAM data, to aid VT ablation ("MRI-aided"), may lead to improved efficacy over traditional EAM-only techniques [12, 17]. The natural evolution of such method may be represented by “MRI-guided” approaches, where EAM acquisition is completely avoided, and the operator relies solely on imaging data; a single-center nonrandomized study demonstrated that this approach is not only feasible and safe, but could lead to lower acute VT inducibility rates and comparable long-term efficacy with “MRI aided” procedures, while allowing more efficient procedures, with lower procedure duration and radiological exposure [9].

The primary objective of this study is to verify, for the first time in a multicenter controlled open-label clinical trial, whether CMR guided and aided strategies, as a whole, truly represent a more effective, more efficient, and at least as safe, if not safer, VT ablation approach when compared to the standard EAM-only guided technique. A confirmation of our primary hypothesis can also lead to the speculation that an imaging-based workflow could better standardize the approach to VT’s substrate, finally determining less variability between operators and a smoother) VT ablation learning curve, as compared to EAM only technique.

While not powered for this specific objective, our study could also reveal whether a complete anatomical CMR-derived substrate elimination, as established for CMR-guided (“Group 1”) procedures, could guarantee better long-term results. The present trial was designed to overcome most of limitations related to the implementation of our proposed approach
. First, the incidence of treatable VA is relatively low in general population and high volume (of cases) is critical for both imaging elaboration and ablation procedures. Accordingly, we created a network of centers, each with at least one major expertise, and a period of training before the trial (6 months) has been devoted to share information about image acquisition and ablation approaches. Eventually, a total of four centers for CMR acquisition and five centers for ablation were able to provide high quality activities, with a definite standardization of CMR sequences and treatment. The most critical process, represented by standardization of imaging acquisition protocols, has been guaranteed and supervised by the core laboratory, in collaboration with the aforementioned external research organization.

In conclusion, VOYAGE is the largest trial so far to propose and test, in a randomized setting, a comprehensive workflow for CMR-guided/aided VT ablation. If positive, results from this study could be applied in large scale in the electrophysiology practice, contributing to the adoption of substrate-tailored approaches, coherently with current trends in the era of precision medicine.

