### Follow-up

Clinical follow-up (FU) will include outpatient clinic visits at 1, 6 and 12 months after the ablation procedure. If no contraindications, amiodarone (if used) should be stopped at the 1-month FU visit. At all follow up visits, the following parameters and information will be taken:Physical examination.12-lead surface ECG.Transthoracic echocardiography (at 6 and 12 months).ICD interrogation, analyzing any event marked as VT or VF by the device.

To assess changes in health-related quality of life, the 36-Item Short Form Survey (SF-36) will be administered at enrolment and at the 12-months follow up visit (Table 4).

**Table 4 Tab4:** Study timeline

PROCEDURE	VISIT						
	Enrollment	Baseline	Ablation	Discharge	1 month	6 months	12 months
Eligibility screen	✓						
Informed consent	✓						
Demographic Data		✓					
Medical History		✓					
QoL assessment		✓					✓
Medication		✓		✓	✓	✓	✓
12-lead ECG		✓		✓	✓	✓	✓
CMR (gr. 1 and 2)		✓					
TTE		✓				✓	✓
Cardiac CT (gr. 1 and 2)		✓					
ICD check				✓	✓	✓	✓
Ablation data			✓				
Safety data			✓	✓	✓	✓	✓
Protocol Deviation	✓	✓	✓	✓	✓	✓	✓
Adverse event	✓	✓	✓	✓	✓	✓	✓
Termination	✓	✓	✓	✓	✓	✓	✓

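### The Discussion makes at-least-as-safe part of the primary objective, but the Methods do not, and the planned difference tests in 103 patients cannot establish it

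*Protocol article*

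**What the plan says.** The protocol article describes the primary objective in two ways.

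- **Methods, Study hypothesis and primary endpoint:** the CMR approaches are to be judged "in terms of effectiveness at 12 months in comparison to a control group (standard of care VT ablation"). Table 1 places procedural time, fluoroscopy, X-ray exposure, radiofrequency measures and 12-month complications among the secondary endpoints. The Abstract also calls efficiency and safety secondary.
- **Discussion:** the primary objective is to verify whether the CMR strategies together "truly represent a more effective, more efficient, and at least as safe, if not safer, VT ablation approach" compared with EAM alone.

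Sample size and statistical analysis states that "103 patients will be necessary with 80% power and 5% type 1 error", based on VT recurrence. It adds: "All applicable statistical tests will be 2-sided and will be performed using a 5% significance level". For complications the rule is: "Categorical variables will be expressed as total number (percentage) and will be compared by chi-squared test". No margin or confidence-limit rule for safety is given.

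Two reporting details bear on the point. The complication list in Table 1 includes "Prolonged or repeat hospitalization" and all deaths over 12 months, without restriction by cause. Table 4 schedules "Cardiac CT (gr. 1 and 2"), while X-ray exposure in Table 1 is not defined.

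**The concern.** At least as safe is a non-inferiority statement. It needs a limit on how much worse the new approach could be, and enough data to exclude that limit. A difference test that fails to reach significance shows neither. If the Discussion wording carries into the final report, a non-significant complication comparison in about 100 patients could be presented as meeting the primary objective.

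Three smaller matters affect the same comparison:

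- Chi-squared is fixed for every categorical variable, including individual complications that are likely to be sparse.
- A readmission for VT is an efficacy failure, yet it can enter the complication list.
- A reader cannot tell whether the radiation comparison counts the preprocedural CT, which is scheduled for the CMR workflow.

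**Working it through.** **Inputs from the protocol article:** N = 103, 50% Groups 1–2 and 50% Group 3 (taken as 52 and 51), recurrence 16% and 44%, HR 2.75, two-sided 5%, 80% power. **Assumed, because the article gives none:** complication rates, unequal splits of 72/31 and 82/21, and the share of recurrences that lead to readmission.

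**1. The plan's own figure.** Events = (1.960 + 0.842)² / (0.25 × ln(2.75)²) = 30.7. The mean event rate is (0.16 + 0.44)/2 = 0.30, and 30.7/0.30 = 102.3, which rounds up to 103. The size reproduces, and it depends on VT recurrence only.

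**2. Precision for safety.** The half-width of the 95% interval with equal rates p is 1.96 × √[p(1−p)(1/52 + 1/51)]. At p = 8% this is 1.96 × 0.0535 = 0.105. It is 6.6 points at 3%, 8.4 at 5% and 11.6 at 10%.

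**3. Chance of detecting a doubled complication rate.** This is an exact enumeration of the uncorrected two-sided chi-squared test at 52 versus 51.

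| Group 3 rate | Groups 1–2 rate | Probability of significant harm |
|---|---|---|
| 3% | 6% | 10% |
| 5% | 10% | 15% |
| 8% | 16% | 24% |
| 10% | 20% | 29% |

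Non-significance is the likely result even when the complication rate doubles.

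**4. What margin 103 patients could exclude.** With equal true rates, one-sided 2.5% and 80% power, the margin is 2.802 × SE: 9.4 points at a 3% rate, 12.0 at 5%, 15.0 at 8% and 16.6 at 10%.

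**5. Sparse tables.** With 10 events in all (10/103 = 9.7%), the expected count in Group 3 is 10 × 51/103 = 4.95, which is below 5. False-positive rates of the uncorrected chi-squared test when both groups have the same true rate, by exact enumeration:

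| Split (Groups 1–2 / Group 3) | 1% | 2% | 5% | 8% |
|---|---|---|---|---|
| 52/51 (planned) | 0.2% | 1.4% | 4.9% | 5.4% |
| 72/31 (assumed) | 2.0% | 3.9% | 4.9% | 4.8% |
| 82/21 (assumed) | 9.0% | 8.9% | 4.8% | 3.5% |

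At 52/51 the errors divide about evenly by direction. At 72/31 and 82/21, with rates of 1–2%, essentially all of them say that Group 3 is worse. At 82/21 a single event, if it falls in Group 3, is enough: χ² = 103 × 82² / (82 × 21 × 1 × 102) = 3.94, above the critical 3.84. At 72/31, a result of 0 versus 2 events gives p = 0.030 uncorrected, 0.16 with continuity correction and 0.089 by Fisher's test.

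**6. Readmissions, if the items were pooled.** Suppose half of recurrences lead to readmission and procedural complications are 10% with CMR and 5% in Group 3. Any complication is then 1 − 0.90 × (1 − 0.16 × 0.5) = 17.2% with CMR and 1 − 0.95 × (1 − 0.44 × 0.5) = 25.9% in Group 3. The direction reverses.

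**The case against.** The operative Methods are clear: effectiveness is primary and the rest is secondary. The conflict lies in one Discussion sentence, and nothing in the article says that a non-significant result will be read as proof of safety. A margin may also stand in an analysis plan that is not shown. All of this is fair, and it makes the repair mainly one of wording. It does not remove the contradiction. A margin elsewhere would still meet the limits in step 4 of the working.

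Several stronger readings are tempting, but the documents do not support them.

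- **Efficiency cannot be tested either.** Procedural time, fluoroscopy duration and radiofrequency time are continuous, and "these variables will be compared using Student’s t-test if normally distributed", with Aspin-Welch or Mann–Whitney otherwise. With 52 versus 51, a difference of 2.802 × √(1/52 + 1/51) = 0.55 SD has 80% power, which is workable. For efficiency only its placement in the primary objective is at fault.
- **CT dose is left out.** X-ray exposure is undefined, so CT is neither included nor excluded, and the full protocol may settle it. Some Group 3 patients may also have been scanned before their images were judged inadequate.
- **Chi-squared inflates error in general.** At the planned split it is conservative for rare events. The 9% figure needs an assumed 82/21 split and rates of 1–2%.
- **Safety is a pooled endpoint contaminated by efficacy.** Table 1 lists the items one by one. The reversal in step 6 occurs only if they are pooled, which the article does not state.
- **Two-sided testing is the fault.** A two-sided 95% interval read against a stated margin would serve.

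**Conclusion.** The point stands in limited form and should be corrected. The Discussion's primary objective contradicts the Methods, and the stated analysis cannot deliver its safety part. At 52 versus 51, a doubling of complications would be detected with probability 10% to 29% for assumed Group 3 rates of 3% to 10%. At an assumed 8%, the interval is ±10.5 points.

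The chi-squared point is smaller. It depends on the split departing from 50/50, which is possible because Trial design fills Group 3 with patients unsuitable for imaging or with inadequate images. At true rates of 1–2%, false positives are then 2–4% at 72/31 and 9% at 82/21, falling against Group 3. These figures use the uncorrected statistic; the article does not say which version applies.

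The same allocation rule means that Group 3 is not a randomised comparator. Better intervals will describe the safety difference honestly, but they will not remove confounding from it.

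**What to change.** - Align the Discussion with the Methods: effectiveness is primary, and safety and efficiency are secondary.
- State that no conclusion of equal or better safety will be drawn from a non-significant test.
- Report complication risk differences with exact 95% confidence intervals.
- Use Fisher's exact test where any expected count is below 5.
- Show procedure-related complications separately from 12-month readmissions and deaths by cause, so that VT readmissions do not enter the safety comparison.
- Report X-ray exposure both with and without the MDCT dose.

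No extra patients are needed. The work is rewording, a few changes to the tables, classifying readmissions and deaths by cause, and copying CT dose from the scan reports. The price is a weaker safety claim and slightly conservative tests.
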